### 2.5. Clinical Decision Support for GPCs

GPs and health staff at participating GPCs will assess real-time PROs via the EPJ, enabling data-driven and individualized consultations. PROs, including physical activity, step count, dietary habits, goal attainment, and smoking status, are automatically transmitted from the patient’s smartphone via the LIVA application and displayed directly within the EPJ. This setup allows GPs and health staff to review lifestyle progress and discuss its implications for T2D management during routine visits.

The CDS tool, developed by Cambio Healthcare Systems A/S, Denmark, provides personalized pharmacological treatment recommendations within the EPJ. It is based on phenotyping and clinical algorithms and aligns with the most recent Danish Society for General Practice guidelines for the treatment of T2D. The CDS tool was co-developed with hospital specialists from Odense University Hospital, Slagelse Hospital, and Holbæk Hospital, and in consultation with GPs.

The CDS system incorporates key clinical parameters, including comorbidities, symptoms, and current medications, all extracted from the EPJ. These variables are processed using validated algorithms to generate evidence-based treatment guidance for hyperglycemia, hypertension, and hypercholesterolemia.

Within three months of inclusion, participants will be scheduled for a GPC visit to evaluate and, if necessary, adjust pharmacological treatment. If treatment targets for glycemic control, blood pressure, or lipid levels are not met, the GP will consider intensifying pharmacological treatment, based on recommendations provided by the CDS. The CDS prioritizes individualized pharmacological treatment to enhance treatment efficacy and minimize adverse effects.

### 2.6. Control Group

Participants assigned to the control group will receive usual care during the first year of the study period, in accordance with current Danish guidelines for the management of T2D. This care may include routine consultations with the GPs or other health staff, and all pharmacological treatment decisions will be made independently of the CDS system during this period.

Although the control group participants will not have access to the LIVA lifestyle coaching application or the CDS tool in the first year, they will undergo the same clinical examinations and complete the same questionnaires as those in the intervention group.

After 12 months, participants in the control group will be offered full intervention, mirroring the services and support provided to the intervention group in the first year.

### 2.7. Patient Examination and Data Sampling

Prior to the initial examination, all participants must provide signed, written informed consent. In Table 1, an overview of the timeline of patient examinations at GPCs and study components during the DICTA trial is provided.

The following parameters will be measured at baseline and at the 12-month follow-up visit: weight, systolic and diastolic blood pressure, and hip and waist circumference. However, height will only be measured at baseline. Blood pressure measurement will follow Danish clinical guidelines, which recommend measurements taken twice daily (morning and evening) over three consecutive days, prior to medication intake. Each session should include three repeated measurements. Whenever possible, these measurements should be conducted in the participant’s home. If the participant does not own a blood pressure monitoring device, one will be provided by the GPC. In both scenarios, the GPC will test and calibrate the blood pressure device during the baseline visit and record all subsequent measurements.

At both baseline and the 12-month follow-up, the following laboratory assessments will be performed: hemoglobin A1c (HbA1c), low-density lipoprotein (LDL) cholesterol from blood samples, and urine albumin/creatinine ratio (UACR) from spot urine samples. Availability of these data is contingent upon the participant’s written consent, which authorizes manual extraction from the EPJ. In Table 2, a detailed description of all the study variables and data sources is provided. All measurements will be conducted by trained clinical staff with prior instruction in standardized assessment techniques to ensure reliability and consistency.

Information regarding prescribed medications will be obtained from the Danish National Prescription Registry. Consent also allows access to the Shared Medication Record, from which information concerning the intended treatment dosage will be manually extracted at both baseline and follow-up.

At baseline, 6 months, and 12 months, the participant will receive a letter via e-Boks (a trusted Nordic provider of secure platforms and digital post boxes) containing a link to a questionnaire. The complete questionnaire battery, consisting of 45 items, is primarily composed of various standardized and validated instruments. For constructs where no validated questions were available, the research team has developed original items. These have been pilot-tested and revised accordingly before being included in the final questionnaire battery. The questionnaire battery covers topics including education level, physical activity, smoking habits, alcohol use, dietary habits, work ability (inspired by WPAI (Work Productivity and Activity Impairment Questionnaire [28])), general health (EQ-5D-5L and EQ-VAS [29]), mental well-being (SWEMWBS (Short Warwick-Edinburgh Mental Well-being scale [30,31])), and e-health literacy (eHLQ [32]-License number: E2019IA). The English version of the complete questionnaire battery is available in Supplementary Material, Table S2.

Much of the data will either be captured electronically or collected during the routine clinical consultations at the GPCs planned as part of the structured management of patients with T2D, thus minimizing the risk of missing data. However, if a GPC forgets to report data, we will have a very close and continuous collaboration with all the participating GPCs giving us the opportunity to make them aware of any forgetfulness. Finally, in case of missing data that cannot be recovered, we will use the “last carrying forward” or “the next carrying backwards” and supplement with sensitivity analyses excluding patients missing the data in focus.

## 3. Outcomes

The primary outcome is the one-year change in estimated ten-year cardiovascular risk assessed by SCORE2-Diabetes calculated from age, smoking status, systolic blood pressure, total and high-density lipoprotein cholesterol, age at diabetes diagnosis, HbA1c, and eGFR [33]. As we will be focusing on one-year changes in SCORE2-Diabetes, we do not consider it a problem that SCORE2-Diabetes does not include prevalent cardiovascular disease in the risk calculation as this variable will be constant over the one-year period on almost all of the patients. A previous Swedish study supports that these risk factors capture most of the residual cardiovascular risk in patients with T2D [34]. The secondary outcomes are group differences in changes between baseline and 12 months of follow-up in the following:Quality of life, measured by EQ-5D-5L;HbA1c, blood pressure, LDL cholesterol, smoking, and UACR;Use of glucose-lowering, antihypertensive, and lipid-lowering medications;Weight and abdominal circumference;Daily physical activity level, measured with AX3 accelerometers.

To support the assessment of the primary and secondary outcomes, a wide range of clinical, biochemical, and behavioral data will be collected throughout the study. Table 2 provides detailed descriptions of all study variables, including their definitions, measurement methods, data types, and sources. Details of the different ICD-10 codes included in this study are provided in Supplementary Material, Table S3.

## 4. Statistics

### 4.1. Power Calculations

In a recent publication using Danish health registries [35], we have calculated that the actual, absolute ten-year risk of cardiovascular disease for the entire DD2 cohort is 12.3%. Generally, 15% relative risk reduction is considered clinically relevant in clinical randomized controlled trials. Therefore, we define the minimal clinically relevant difference as 15% of 12.3%, which is approximately 2%. With a standard deviation of 4%, statistical power set at 90%, and a significance level of 5%, the study will require a sample size of at least 130 patients in both the intervention and the control group. Based on DD2 data [35], we expect approximately 20% of the participants to have prevalent cardiovascular disease and we anticipate 10–15% dropouts, therefore we will include 400 patients in total.

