## 2. Materials and Methods

### 2.1. Study Design

The DICTA study is a two-arm, cluster-randomized controlled trial (RCT) and will be conducted across multiple general practitioner clinics (GPCs) in Denmark. A randomization list will be generated using the program “sealedenvelope”, and cluster-randomization will occur at the GPC level, with an allocation ratio of 2:3 (intervention: control) and variable block sizes of 5 and 10 to ensure the balance between the two groups. Our allocation ratio of 2:3 is chosen based on an expectation that recruiting patients into the control group will be more challenging due to lower engagement incentives. Stratification will be based on two factors to ensure equal quality of care and no change in information sharing between study groups. Firstly, the GPC’s participation in the “Specialist supervised individualised multifactorial treatment of new clinically diagnosed type 2 diabetes in general practice (IDA): a prospective controlled multicentre open-label intervention study” [25] will be taken into consideration. Secondly, the physical address of the GPC will be considered. This is because some GPCs share address and health staff, and other GPCs operate as solo practices and thereby reduce the risk of intervention-based guidance of the control group patients. Other aspects such as age and gender of GPs, have not been taken into account as differences in quality of care is small and it is not possible to stratify on this. In Figure 1, the overview of the study’s elements is illustrated for both the intervention and control groups.

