### 4.2. Analysis

In general, categorical variables will be summarized as numbers (%), continuous variables as min–max, mean (standard deviation, SD), and median (interquartile range, IQR), by randomization group.

The primary analysis of the primary outcome will follow an intention-to-treat principle, but due to the definition of the primary outcome, only participants with relevant measurement available at both baseline and one year of follow-up. We will employ a logistic regression model with robust variance estimation, accounting for GP clustering. As a secondary analysis approach, we will model the count of risk factors at both baseline and at one year of follow-up in a population-averaged longitudinal regression model based on generalized estimation equations (GEE), where group differences are included as a time-by-group interaction term. This approach accounts for clustering and potential missing measurements at each time point and will not be restricted to complete observations.

The analysis of the secondary outcomes will follow these two approaches outlined above. To generate hypotheses, several exploratory post hoc analyses will be conducted. The level for statistical significance is set at 5%. We will use statistical software such as StataBE (version 18.5 or newer) or R (version 4.5.1 or newer) for analysis.

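### Section 4.1's inputs require 85–86 patients per group, not 130, and neither clinic randomisation nor 2:3 allocation enters the calculation, so the stated 90% power cannot be verified

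*Protocol article*

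**What the plan says.** The outcome being powered is a change score. Protocol article, section 3 (Outcomes): "The primary outcome is the one-year change in estimated ten-year cardiovascular risk assessed by SCORE2-Diabetes".

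Section 4.1 (Power Calculations) sets the target: "we define the minimal clinically relevant difference as 15% of 12.3%, which is approximately 2"%. It then gives the remaining inputs, "With a standard deviation of 4%, statistical power set at 90%, and a significance level of 5"%, and concludes that a minimum of 130 patients is needed in each of the two groups. After that it adds about 20% with prevalent cardiovascular disease (CVD) and 10–15% dropout, and arrives at 400 patients in total.

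Elsewhere the design is clustered and unequal. Section 2.1 (Study Design) states that "cluster-randomization will occur at the GPC level", in a 2:3 ratio of intervention to control. Section 2.2 expects about 70 clinics. Section 4.2 (Analysis) plans a model "with robust variance estimation, accounting for GP clustering". Section 4.1 gives no intracluster correlation (ICC), cluster size or design effect, and does not use the 2:3 ratio.

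**The concern.** Section 4.1 prints a full chain of difference, SD, power and significance level, followed by a sample size. The sample size does not follow from the chain. The gap is not small (130 against 85), and the text attributes it to nothing.

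Two features of the design that should enter the calculation are also missing from it: randomisation by clinic and unequal allocation. A reader therefore cannot tell whether 130 already contains a cluster allowance, rests on a different SD, or is a slip. At stake is the interpretation of the result. If the trial is neutral, readers will ask what difference it could have detected, and the printed 90% cannot be traced to any set of stated assumptions.

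**Working it through.** **Inputs from section 4.1:** difference 2 points (unrounded 0.15 × 12.3 = 1.845); SD 4 points; power 90%; significance 5%, taken as two-sided because the article does not say; 130 per group; losses of 20% and 10–15%; total 400. **From sections 2.1 and 2.2:** clinics allocated 2:3, about 70 clinics.

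**1. Reproducing the 130.** For two means with equal arms, n per group = 2 × SD² × (1.960 + 1.282)² / difference².

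- Difference 2: 2 × 16 × 10.507 / 4 = 84.06, so 85. The exact t-test gives 85.03, so 86.
- Difference 1.845: 2 × 16 × 10.507 / 3.404 = 98.8, so 99. The t-test gives 99.7, so 100.

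Variants that keep the stated difference, SD, power and significance level also fail:

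| Variant | Intervention / control |
|---|---|
| One-sided, difference 2 | 69 / 69 |
| One-sided, difference 1.845 | 81 / 81 |
| 2:3 allocation, difference 2 | 71 / 106 |
| 2:3 allocation, difference 1.845 | 83 / 124 |

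Reading SD 4 as the SD of a single score and multiplying it by √2 gives 169 per group. None of these is 130.

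**2. Power at 130 per group, individuals randomised.** Normal approximation: 98.1% for 2 points and 96.1% for 1.845 (t-test: 98.0% and 95.9%). The printed figure is 90%.

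**3. What would produce about 130.**

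- An SD of 4.97 instead of 4 (SD 5 gives 132).
- A design effect of 130/85 = 1.53, or 130/100 = 1.30 for 1.845.
- Power of 95% with 2:3 allocation: 87 intervention and 130 control, so only the larger arm reaches 130.
- Losses applied to 85: 85/(1 − 0.35) = 131. This would use the losses twice, because 260/(1 − 0.20 − 0.15) = 400 already accounts for the total.

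The article states none of these.

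**4. Arm sizes under 2:3.** If patients split as clinics do, 400 become 160 and 240. After 35% loss, 160 × 0.65 = 104 and 240 × 0.65 = 156. With the mildest reading of the stated losses (20%, then 10% of the rest), the intervention arm is 160 × 0.80 × 0.90 = 115, still below 130. If patients with prevalent CVD are analysed and only 15% drop out, the arms are 136 and 204, and both exceed 130.

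**5. Illustration of clustered power.** The article gives no ICC and no cluster-size variation. I assume ICC 0.01–0.10, a coefficient of variation (CV) of cluster size of 0–0.8, and a comparison of means. Design effect = 1 + ((1 + CV²) × m − 1) × ICC, and power = Φ(difference / (4 × √((1/n₁ + 1/n₂) × design effect)) − 1.960).

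| Evaluable | m per clinic | ICC, CV | Design effect | Power, 2 points | Power, 1.845 |
|---|---|---|---|---|---|
| 104 + 156 | 260/70 = 3.71 | 0.01, 0 | 1.03 | 97.4% | 94.9% |
| 104 + 156 | 3.71 | 0.05, 0.8 | 1.25 | 94.1% | 90.2% |
| 104 + 156 | 3.71 | 0.10, 0.8 | 1.51 | 89.5% | 84.3% |
| 136 + 204 | 340/70 = 4.86 | 0.01, 0 | 1.04 | 99.3% | 98.3% |
| 136 + 204 | 4.86 | 0.10, 0.8 | 1.70 | 93.4% | 89.2% |

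At 104 versus 156, power is exactly 90% when the design effect is (2/4)² / ((1/104 + 1/156) × 10.507) = 1.48. For 1.845 points the corresponding value is 1.26.

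**The case against.** A reader might infer that the 90% is wrong, or that the trial is underpowered. The article supports neither. The stated sample size is larger than its inputs require, so before clustering the discrepancy is conservative. A cluster allowance of about 1.53 may sit unstated inside the 130, in which case 90% would be the clustered power. That factor corresponds to an ICC of about 0.11 at 400/70 = 5.7 patients per clinic, or about 0.20 at 3.7. The illustrative range above stays at about 90% or higher for the 2-point target. It falls to 84% only when the smaller difference, the highest assumed ICC and the most uneven clinics are combined.

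Other points on that side also stand:

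- The rounding from 1.845 to 2 is disclosed, since both factors are printed. It matters (2/12.3 is a 16.3% reduction, and keeping 1.845 raises n by about 18%), but nothing is concealed.
- An ICC and cluster sizes are details that an article may leave to the full protocol or analysis plan. Their absence alone would not be a finding.
- The 2:3 ratio applies to clinics and was chosen because control patients were expected to be harder to recruit. The patient split may therefore end up closer to equal than 104 versus 156.
- Whether patients with prevalent CVD leave the analysis is unclear. Section 4.1 counts them as a loss, section 3 says prevalent disease is not a problem for a change score, and section 4.2 restricts only to patients measured at both times.
- The check uses a comparison of means, whereas section 4.2 names logistic regression, so the clustered figures are illustrations and not the power of the planned model.

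None of this closes the gap between the printed inputs and the printed 130. That is a misstatement in the article itself, not detail left to another document.

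**Conclusion.** Section 4.1 is internally inconsistent. The 130 per group is 53% above the 85 that the inputs give (130/85 = 1.53) and 30% above the 100 for the unrounded difference. The losses for CVD and dropout do not explain it. The equal minimum for both arms does not match the 2:3 allocation: if patients split in that ratio and both stated losses apply, the intervention arm has about 104–115 patients.

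The supported conclusion is that the 90% cannot be verified from what is stated, and no more than that. The sample size mismatch rests on the article's own figures and a two-sided test; a one-sided test widens it. The clustered power ranges, about 97–90% for 2 points and 95–84% for 1.845 with 260 evaluable, and about 99–93% and 98–89% with 340, rest on assumed ICC and CV values.

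**What to change.** Restate section 4.1 so that inputs and result agree. It should give:

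- the difference actually used, 2 or 1.845 points;
- whether SD 4 is the SD of the one-year change or of the score at one time;
- whether the test is two-sided;
- the expected number of patients per arm under 2:3 clinic allocation, in place of one minimum for both arms;
- whether patients with prevalent CVD are in the primary analysis, consistently with sections 3 and 4.2;
- the ICC, mean cluster size and design effect behind 130, with the resulting power, preferably over a range of ICC values.

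If 130 came from another input, such as an SD near 5, correct that input. The cost is one recalculation and a change of wording. No extra patients are needed.

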### 4.2. Analysis

In general, categorical variables will be summarized as numbers (%), continuous variables as min–max, mean (standard deviation, SD), and median (interquartile range, IQR), by randomization group.

The primary analysis of the primary outcome will follow an intention-to-treat principle, but due to the definition of the primary outcome, only participants with relevant measurement available at both baseline and one year of follow-up. We will employ a logistic regression model with robust variance estimation, accounting for GP clustering. As a secondary analysis approach, we will model the count of risk factors at both baseline and at one year of follow-up in a population-averaged longitudinal regression model based on generalized estimation equations (GEE), where group differences are included as a time-by-group interaction term. This approach accounts for clustering and potential missing measurements at each time point and will not be restricted to complete observations.

The analysis of the secondary outcomes will follow these two approaches outlined above. To generate hypotheses, several exploratory post hoc analyses will be conducted. The level for statistical significance is set at 5%. We will use statistical software such as StataBE (version 18.5 or newer) or R (version 4.5.1 or newer) for analysis.

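### The primary analysis is a logistic regression and its backup models a count of risk factors, but the primary outcome is a continuous change in SCORE2-Diabetes, so neither estimates the effect the trial is powered for

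*Protocol article*

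**What the plan says.** Section 3 (Outcomes) of the protocol article: "The primary outcome is the one-year change in estimated ten-year cardiovascular risk assessed by SCORE2-Diabetes". The abstract gives the same definition. Neither place states a threshold or a responder category.

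Section 4.1 (Power Calculations): "we define the minimal clinically relevant difference as 15% of 12.3%, which is approximately 2" per cent. It continues: "With a standard deviation of 4%, statistical power set at 90%, and a significance level of 5" per cent, "the study will require a sample size of at least 130 patients in both the intervention and the control group".

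Section 4.2 (Analysis), on the primary analysis of the primary outcome: "We will employ a logistic regression model with robust variance estimation, accounting for GP clustering". On the secondary approach, a GEE with a time-by-group interaction: "we will model the count of risk factors at both baseline and at one year of follow-up". On everything else: "The analysis of the secondary outcomes will follow these two approaches outlined above".

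Table 2 types HbA1c, blood pressure, LDL cholesterol, UACR, weight, waist circumference and accelerometer activity as continuous.

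**The concern.** The outcome, the power calculation and the model should all refer to one quantity. Here the first two refer to a difference in mean change, in percentage points. The primary model returns an odds ratio for a binary variable that has not been defined. The backup returns a difference in the change of a count that appears neither among the outcomes nor in Table 2.

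An analyst following the text must either depart from it or choose a cut-off for the change in SCORE2-Diabetes. A cut-off chosen once data are in hand is open to selection on the result. The resulting odds ratio could not be judged against the 2-point difference that the article calls clinically relevant, and dichotomising discards information.

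**Working it through.** **1. The three sections side by side**

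| Element | Place | Scale |
|---|---|---|
| Primary outcome | Section 3 | Continuous change, percentage points |
| Effect used for power | Section 4.1 | Difference of about 2 points, SD 4: a comparison of means |
| Primary model | Section 4.2 | Logistic: binary outcome, odds ratio |
| Second model | Section 4.2 | GEE on a count of risk factors |

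Nothing in the article links the continuous change to a binary variable or to a count. The mismatch is complete at this point; the arithmetic below only illustrates its cost.

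**2. The plan's own sample size.** Inputs from section 4.1: difference δ = 2 (unrounded, 0.15 × 12.3 = 1.845), SD 4, power 90%, α 5%. I take α as two-sided, the SD as that of the change, and equal groups without clustering.

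n per group = 2 (1.960 + 1.282)² × SD² / δ², with (1.960 + 1.282)² = 10.507.

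- δ = 2: 2 × 10.507 × 16 / 4 = 84.06, so 85.
- δ = 1.845: 2 × 10.507 × 16 / 3.404 = 98.8, so 99.

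The stated 130 in both groups is not reproduced. That is a separate matter and does not affect this point. The inputs are those of a comparison of means under any variant.

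**3. Power of a comparison of means at the stated 130 per group.** Power = Φ(δ / (SD √(2/n)) − 1.960).

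- δ = 2: Φ(4.031 − 1.960) = 98.1%.
- δ = 1.845: Φ(3.719 − 1.960) = 96.1%.

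**4. If the change were dichotomised so that a logistic model could be fitted.** Assumptions: normal change with SD 4, control mean change 0, and response defined as a change at or below a cut-off c. The article gives no cut-off, so c runs from 0 to −4 points. Then p₀ = Φ(c/4) and p₁ = Φ((c + δ)/4). With p̄ the mean of the two,

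n = [1.960 √(2p̄(1−p̄)) + 1.282 √(p₀(1−p₀) + p₁(1−p₁))]² / (p₁ − p₀)².

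| δ | c | p₀ | p₁ | n per group for 90% | Power at 130 per group |
|---|---|---|---|---|---|
| 2 | 0 | 0.500 | 0.691 | 136 | 88.7% |
| 2 | −1 | 0.401 | 0.599 | 133 | 89.4% |
| 2 | −2 | 0.309 | 0.500 | 136 | 88.7% |
| 2 | −4 | 0.159 | 0.309 | 166 | 81.9% |
| 1.845 | 0 | 0.500 | 0.678 | 160 | 83.3% |
| 1.845 | −1 | 0.401 | 0.584 | 156 | 84.1% |
| 1.845 | −2 | 0.309 | 0.485 | 161 | 83.1% |
| 1.845 | −4 | 0.159 | 0.295 | 197 | 75.0% |

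The row c = 0 is a split at the control median. The ratio 85/136 = 0.625 agrees with the large-sample efficiency of a median split, 2/π = 0.637.

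**5. The same median split at the planned enrolment.** Section 2.1 fixes the design "with an allocation ratio of 2:3 (intervention: control) and variable block sizes of 5 and 10", and section 4.1 enrols 400 with 10–15% dropout, leaving 340 to 360 evaluable. If the expected 20% with prevalent cardiovascular disease were also left out, 272 to 288 would remain. Without clustering:

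| Evaluable (2:3) | Median split, δ = 2 | Median split, δ = 1.845 | Means, δ = 2 | Means, δ = 1.845 |
|---|---|---|---|---|
| 340–360 | 94–96% | 91–92% | 99–100% | 99% |
| 272–288 | 89–90% | 83–85% | 98–99% | 96–97% |

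**The case against.** The strongest objections are these.

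- **The power loss is hypothetical.** No median split is planned, and 130 per group is not the actual design. At 2:3 with 340 to 360 evaluable, even a median split keeps 91–96% power. This stands: the power figures are an illustration under an assumed cut-off and should not carry the severity. The mismatch does not depend on them.
- **A logit model need not imply a binary outcome.** SCORE2-Diabetes is itself a predicted probability, so a fractional logit could be fitted to the 12-month risk and converted to percentage points. The article does not say this, and such a model cannot be fitted to a change score that takes negative values, which is the outcome defined.
- **The GEE structure is sound.** True: a clustered model with a time-by-group interaction suits a difference in one-year change. Only the variable named is wrong, but that is enough for it not to address the primary outcome.
- **Some secondary outcomes do suit logistic models.** True of smoking and medication use, and Table 2 types EQ-5D-5L as categorical. The carry-over sentence might also mean only a complete-case and a longitudinal approach. Even so, no suitable model is then named for HbA1c, blood pressure, LDL cholesterol, UACR, weight, waist or accelerometer activity.
- **The article is condensed.** The full protocol or SAP may name the right model, in which case this is an error in the article. But condensing would leave a model out; it would not name an incompatible one. A slip of logistic for linear would not explain the count in the next sentence. The article does not say where either model came from.

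**Conclusion.** The point holds and must be corrected before analysis. As published, the primary outcome has no valid prespecified analysis: section 4.2 names a model for a binary variable that is never defined, with a backup on a count that is not an outcome. Neither estimates the 2-point mean difference in section 4.1. This conclusion rests on the wording of sections 3, 4.1 and 4.2 alone.

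The size is conditional on a normal change with SD 4, a control mean change of 0, no clustering and an assumed cut-off between 0 and −4 points. At 130 per group, power would be 82–89% instead of 98% for 2 points, and 75–84% instead of 96% for 1.845 points. At the planned enrolment the loss is smaller. The larger harm is an effect measure that cannot be compared with the stated relevant difference, and a cut-off left open to choice after the fact.

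**What to change.** Rewrite section 4.2, and bring the SAP into line with it:

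- Primary analysis: a linear model for 12-month SCORE2-Diabetes (or its change) with arm and baseline score as covariates, and either clinic-clustered robust standard errors or a clinic random intercept. Report the mean difference in percentage points with a 95% confidence interval.
- Longitudinal analysis: keep the GEE with its time-by-group interaction, but with SCORE2-Diabetes at baseline and 12 months as the dependent variable.
- Secondary outcomes: linear models for continuous measures, with UACR on the log scale; logistic models only for binary ones such as smoking and medication use. State how EQ-5D-5L is scored and model it accordingly.
- If a binary primary outcome is in fact intended, define and justify the cut-off and redo the power calculation on that scale.

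Removing the contradiction requires only that model and outcome agree. Baseline adjustment, the choice between robust errors and a random intercept, and the log scale are recommendations within that. The cost is wording in section 4.2 and the SAP, settled before any comparison by arm; no data or patients are affected.
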